## Abstract

Physical inactivity is one of the major modifiable lifestyle risk factors for cardiovascular disease (CVD). This protocol aims to evaluate the effectiveness of Tai Chi versus brisk walking in reducing CVD risk factors. This is a randomized controlled trial with three arms, namely, Tai Chi group, walking group, and control group. The Tai Chi group will receive Tai Chi training, which consists of two 60-min sessions each week for three months, and self-practice for 30 min every day. The walking group will perform brisk walking for 30 min every day. The control group will receive their usual care. 246 subjects with CVD risk factors will be recruited from two outpatient clinics. The primary outcome is blood pressure. Secondary outcomes include fasting blood for lipid profile, sugar and glycated haemoglobin (HbA1c); body mass index, waist circumference, body fat percentage; perceived stress level and quality of life. Data collections will be conducted at baseline, 3-month, 6-month and 9-month. Generalized estimating equations model will be used to compare the changes in outcomes across time between groups. It is expected that both the Tai Chi and walking groups could maintain better health and have improved quality of life, and that Tai Chi will be more effective than brisk walking in reducing CVD risk factors.

## 1. Introduction

According to the World Health Organization [1], an estimated 17.3 million people died from cardiovascular diseases (CVD) in 2008. By 2030, more than 23 million people will die annually from CVD. In Hong Kong, CVD is the fourth leading cause of death, and more than 3000 people die from CVD each year [2]. The prevalence of CVD risk factors is rapidly increasing in developing and developed countries. Individuals with CVD risk factors have a twofold chance of death, threefold chance of developing CVD, and fivefold chance of suffering from type 2 diabetes mellitus [3]. This development imposes a significant health burden on society. Therefore, CVD is clearly an important and common public health problem, and preventive measures need to be implemented to minimize the risk factors contributing to CVD.

The core CVD risk factors include hypertension, hyperglycemia, dyslipidemia, and obesity [4]. Psychosocial stressors affect the quality of life and associate with increased CVD risk factors [5]. Physical inactivity is one of the major lifestyle risk factors for CVD [1]. Staying physically active is always recommended because regular physical exercise can increase insulin sensitivity, improve lipid levels, lower blood pressure (BP), reduce weight, and lower the risk of CVD [3].

In Hong Kong, the Behavioural Risk Factor Survey conducted by the Department of Health in April 2010 found that the level of physical activity of the residents was clearly not enough for optimal health gain [6]. Studies have shown that interventions to promote regular physical activity are cost-effective in the prevention and the control of CVD risk factors [7]. For a home program, walking is usually adopted for exercise training. Walking has the potential to play a key role in the prevention of CVD [8]. Studies have indicated that the physical benefits of walking are related to consistent adherence and regular exercise. However, adherence to regular walking is still inadequate [7,9]. Among the different types of exercise practiced in the community, Tai Chi can prevent and control CVD risk factors because of its advantages for promoting health. Moreover, participants are relatively more compliant to regular Tai Chi exercise [10].

Tai Chi is a form of martial arts that originated in China in the 16th century. Tai Chi is a therapeutic exercise based on Chinese medicine, and the practice involves the recognition, development, and use of *Qi*. According to the traditional Chinese medicine (TCM) theory, *Qi* is the fundamental energy that sustains life. One purpose of Tai Chi is to balance Yin and Yang and to promote good circulation of *Qi* in the body. A variety of cardiopulmonary fitness indicators has been examined for Tai Chi. Research has demonstrated that Tai Chi has beneficial effects on patients with heart disease [11], metabolic control in type 2 diabetes [12], and on the reduction of BP [13], and emotional stress [14]. Cardiopulmonary benefits of Tai Chi may be partially explained as a response to aerobic exercise. Studies have shown that Tai Chi can be classified as moderate exercise because its intensity does not exceed 55% of maximal oxygen intake [15].

Tai Chi has a long history and is popular among the Chinese population. Therefore, it may be perceived as more culturally appropriate for the Chinese people than other forms of conventional exercise. Tai Chi is a self-learned skill and is easily accessible in the community. Once Tai Chi is learned, people can perform it conveniently at any time and at any place without the need for supervision. From a social perspective, given the ever-rising costs in the healthcare system, adopting a low-cost behavioral modality to promote health and to prevent illnesses is particularly attractive.

Today, health benefits from practicing Tai Chi have gained attention. The focus is not only on how it can alleviate the signs and symptoms of chronic diseases and psychological illnesses, but also on how it can prevent the development of chronic diseases and promote health. Although there are literatures showing that Tai Chi has beneficial effects on people with cardiovascular risk factors [16,17,18], a recent review by Hartley et al. [19] identified 13 trials using Tai Chi for primary prevention of CVD. Authors pointed out that there were some suggestions of beneficial effects of Tai Chi on CVD risk factors but this was not consistent across all studies. Most trials were relatively small (*n* ≤ 88) and short term (≤6 months). They concluded that the effectiveness of Tai Chi for the primary prevention of CVD risk factors was inconclusive [19].

For a home program, walking is usually adopted for exercise training. However, adherence to regular brisk walking is still inadequate [7]. Hence, current literature lacks evidence to support the sustaining beneficial effects of brisk walking on CVD risk reduction. Tai Chi is a safe exercise that requires an energy expenditure that is similar to brisk walking [20]. However, Tai Chi is not known to provide the same cardiovascular training effect as brisk walking. Comparing the health benefits between Tai Chi and brisk walking, particularly to people with CVD risk factors, have been rarely studied in healthcare research. To address the gaps of knowledge, this study aims to compare the effects of Tai Chi with brisk walking in reducing modifiable CVD risk factors. If Tai Chi is as good as or even better than regular brisk walking, this would be of considerable public health importance as it is socially acceptable and attractive and might well be better taken up and sustained than brisk walking.

## 2. Materials and Methods

### 2.1. Subjects

Potential subjects will be recruited from two outpatient clinics. Informed consent will be obtained from every eligible patient who agrees to participate.

Inclusion criteria: Subjects who:
(1)Have systolic blood pressure (SBP) > 140 mmHg or diastolic blood pressure (DBP) > 90 mmHg or are taking blood pressure medication, and(2)Meet at least two but not more than three of the following CVD risk factors that are defined according to the American Heart Association [4]:
(a)Males older than 45 years(b)Females older than 55 years or postmenopausal(c)Smoker(d)Fasting cholesterol level > 6.2 mmol/L(e)Have diabetes or taking medicine to control blood sugar(f)Physically inactive (get <30 min of physical activity for at least 3 days a week)(g)Body mass index (BMI) >25 kg/m^2^ or waist circumference ≥90 cm (men) or ≥80 cm (women)

The reason for limiting the CVD risk factors to two but not more than three is to minimize the heterogeneity of subjects. If subjects are included with any CVD risk factors, this will produce some heterogeneity in the sample, with some having more risk factors than others, which may impact the results.

Exclusion criteria: Subjects who:
(1)Have developed cardiovascular disease(2)Suffered from severe sensory or cognitive impairment(3)Cannot walk independently(4)Have musculoskeletal disorders or other disabling diseases that may limit the practice of Tai Chi(5)Have previous training and practiced Tai Chi within six months prior to the commencement of the study

### 2.2. Study Design

This study will employ randomized controlled trial. Potential subjects will be randomized to enter one of the three groups, namely, Tai Chi, walking, and control. A pilot study has been conducted to test the feasibility of the recruitment process, data collection process, study instruments and intervention process. Interrater reliability test among research assistants was also performed to ensure consistency of the data collection process. Twenty-five participants were recruited for the pilot study. The recruitment process lasted for five weeks (20 participants per month) and it went smoothly. Participant responses toward the data collection instruments generally indicated that the questionnaires were understandable and that the physiological tests were easy to perform.

#### Sample Size and Randomization

A previous study conducted in the Asia-Pacific region reported that SBP is an important marker of risk of CVD in people with and without diabetes. A given reduction in SBP is likely to have similar relative effect on reducing the risk of a cardiovascular event, regardless of diabetes status [21]. SBP is therefore being set as the primary outcome and for sample size calculation.

A previous local study on a Tai Chi program reported a mean reduction of 15.6 mmHg (standard deviation, SD = 7.9) in the intervention group and a mean increase of 6.4 mmHg (SD = 10.5) in the control group [22]. Another pre-post study showed a mean reduction of 8.7 mmHg (SD = 15.6) in SBP after receiving a walking program in obese postmenopausal women [23]. We based our sample size calculation conservatively on discriminating among a mean SBP reduction of 15.5 mmHg in the Tai Chi group, 4.0 mmHg in the control group, and 9.75 mmHg (the grand mean) in the walking group. Further conservatively assuming an SD of 20.0, G*Power gives that 61 subjects per arm will be needed to achieve a power of 80% at a significance level of 5%. To further take into account a potential attrition rate of 25% [12], 246 subjects (82/arm) will be targeted.

A computer-based randomizer will be used for random allocation of subjects [24]. Eligible subjects will be randomly assigned to the three groups in 1:1:1 ratio according to their sequence of enrolment into the study and the corresponding sequentially listed group identifiers generated by the randomizer in advance. The random group identifiers list will be stored in a password-protected computer and only be accessible by the staff who are responsible for group allocation.

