### 2.4. Outcome Measurements

#### 2.4.1. Primary Outcomes

(a)BP: Two measurements of BP will be measured from the seated position after the participant has rested for 10 min. The average of the two values will be used for study purposes. SBP and DBP will be recorded. Only one digital blood pressure monitor will be used for all BP measurements for all participants. Coefficients of variation (CV) of SBP and DBP were reported <10% in a previous study [22]. CV is a unit-less measure that depicts the size of the SD relative to its mean.

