### 2.6. Data Analysis

(1)For demographic data, frequency and percentage will be used to summarize and present categorical variables, whereas mean and SD will be used for continuous variables. Normality of continuous variables will be examined using skewness and kurtosis statistics and normal probability plot. The baseline characteristics among the three groups will be compared using chi-square test and one-way analysis of variance (ANOVA).(2)Generalized estimating equations (GEE) models with appropriate link function and distribution assumption, will be used to compare the changes in outcome variables across time among the three groups with adjustment for those baseline characteristics showing statistically significant differences among the groups. In the GEE model for each outcome, two dummy variables will be set to correspond the three groups with the control as reference. Another three dummy variables will be set to represent the four time points (T1 to T4) with the baseline (T1) as the reference. The interaction-terms of group by time will also be included in the GEE models to assess the differential changes of the outcomes across time and between group. All primary and secondary outcomes will be compared between the three groups on the basis of the intention-to-treat (ITT) principle. The GEE model can account for intra-correlated repeated measures data and accommodate missing data caused by dropouts, provided the data is missing at random [34], and thus is particularly suitable for ITT analysis, without the need for imputation of missing data.

All data analyses will be performed using the latest version of IBM SPSS (IBM Corp., Armonk, NY, USA). Level of statistical significance will be set at 0.05.

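### The primary outcome is SBP in the sample size section but blood pressure (SBP and DBP) elsewhere, and the analysis section names no deciding test that matches the sample size

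*Protocol article*

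**What the plan says.** **Primary outcome.** Three places in the protocol article describe it.

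- Section 2.2, Sample Size and Randomization, argues from SBP as a marker of CVD risk and concludes: "SBP is therefore being set as the primary outcome and for sample size calculation".
- The Abstract says: "The primary outcome is blood pressure".
- Section 2.4.1, under the plural heading Primary Outcomes, has the single item BP and states: "SBP and DBP will be recorded".

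**Sample size (Section 2.2).** It rests on SBP alone. The assumed mean reductions are 15.5 mmHg (Tai Chi), 9.75 mmHg (walking) and 4.0 mmHg (control). The spread is set by "Further conservatively assuming an SD of 20.0". This yields 61 per arm for 80% power at 5%, raised to 82 per arm (246 in total) for 25% attrition.

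**Analysis (Section 2.6).** Each outcome gets a GEE model with two group dummies (control as reference), three time dummies (T1 as reference) and their products: "The interaction-terms of group by time will also be included in the GEE models to assess the differential changes of the outcomes across time". On the error rate it says: "Level of statistical significance will be set at 0.05". It singles out no visit, contrast or joint test as the one that decides the primary question.

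**The concern.** A reader cannot tell from the article whether a DBP result could support the primary claim. The section that gives a reason for its choice says SBP. The section that formally lists primary outcomes, and the abstract, say blood pressure. This is a conflict between statements in the document, not a detail left for an analysis plan.

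Section 2.6 makes the conflict matter more. Three post-baseline visits times two group dummies give six interaction coefficients per outcome. The contrast in the study's stated aim, Tai Chi versus brisk walking, is not one of them because control is the reference, so it adds three more comparisons per outcome. The trial was sized on something simpler: one comparison of three SBP means. If the deciding outcome, visit and contrast are still open when results are seen, the 5% used for the sample size need not be the error rate attached to the primary claim.

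**Working it through.** **1. Reproduce the sample size.** Inputs from Section 2.2: means 15.5, 9.75 and 4.0; SD 20; three equal groups; alpha 0.05. The article does not name the G*Power routine, so a one-way three-group F test is tried.

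- Deviations from the grand mean of 9.75 are +5.75, 0 and -5.75.
- Mean squared deviation = (33.0625 + 0 + 33.0625)/3 = 22.04; square root = 4.695.
- f = 4.695/20 = 0.2347.
- Noncentrality = 3n f². For n = 61 this is 183 × 0.0551 = 10.08, with 2 and 180 degrees of freedom.
- Power is 79.8% at n = 59, 80.5% at n = 60 and 81.2% at n = 61.

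The stated 61 is reproduced to within one subject per arm. Attrition: 61/0.75 = 81.3, rounded up to 82; 3 × 82 = 246. The sample size is sound for one omnibus SBP comparison.

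**2. Count the comparisons that Section 2.6 opens.**

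- SBP, contrasts with control: 3 visits × 2 = 6
- SBP, all three contrasts: 3 × 3 = 9
- SBP and DBP, contrasts with control: 12
- SBP and DBP, all three contrasts: 18

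**3. Error rate if each were tested alone and any p < 0.05 counted.** With independent tests, 1 - 0.95^6 = 26.5% and 1 - 0.95^18 = 60.3%. The tests are not independent: contrasts share arms, visits share patients, and SBP and DBP move together. The article gives no correlations, so they are assumed: 0.3 to 0.7 between changes at different visits and 0.5 to 0.7 between SBP and DBP. Simulating trials with no effect in any arm (200,000 draws per setting) and counting any |z| > 1.96 gives:

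| Tests | Correlations 0.3-0.7 over time, 0.5-0.7 SBP-DBP | Wide grid, 0 to 0.9 |
|---|---|---|
| SBP, 6 | 19-24% | 15-25% |
| SBP, 9 | 25-31% | 20-32% |
| SBP and DBP, 12 | 30-39% | 20-44% |
| SBP and DBP, 18 | 38-49% | 26-54% |

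**4. Error rate under other rules.**

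- One joint group-by-time test for SBP: 5%.
- One joint test each for SBP and DBP, either counting: at most 1 - 0.95² = 9.75%.
- SBP at one named visit, any of three pairwise contrasts: about 12.3%.
- SBP at one named visit, one named test: 5%.

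**5. Power of the pairwise contrasts on the protocol's own figures** (two-sided 0.05, normal approximation, 61 per arm). Standard error = 20 × √(2/61) = 3.62 mmHg.

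- Tai Chi versus walking: 15.5 - 9.75 = 5.75 mmHg; 5.75/3.62 = 1.59; power = Φ(1.59 - 1.96), about 35%. With all 82 per arm retained it is 45%. For 80% power, 190 per arm would be needed.
- Tai Chi versus control: 15.5 - 4.0 = 11.5 mmHg; power about 89%.

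**The case against.** A reader might infer that the plan's primary false-positive rate simply is somewhere between 20% and 50% instead of 5%. The documents do not support that. Section 2.6 does not say that each coefficient is tested on its own, or that any one significant term counts as success. Its wording fits a joint group-by-time test equally well, and the sample size, built on separating three means, points towards an omnibus comparison. The correlations are assumptions too. This objection stands, so the figures in step 3 are conditional.

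It is also fair to say that DBP is weakly placed as a co-primary outcome. Section 2.4.1 has one item, BP, and its sentence on SBP and DBP describes measurement. No separate DBP hypothesis is stated. If the sample size section governs, the 12- and 18-test figures fall away. But the article does not say which section governs, and the abstract does not name SBP either.

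Finally, the primary visit, the contrast and any multiplicity rule may be settled in an analysis plan that is not shown. Their absence from an article is not in itself a fault. That does not remove the conflict over the primary outcome, which lies within the article. A joint interaction test would not settle everything either: pooled over three visits, it is not the single three-group comparison that reproduces the sample size, and it does not show which groups differ or when.

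**Conclusion.** The concern holds in limited form. The primary outcome is stated inconsistently, and the model in Section 2.6 offers six to nine comparisons per outcome at an unadjusted 0.05, while the sample size corresponds to one omnibus SBP test.

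The inconsistency is certain because it is on the page. Its effect on the error rate is not fixed by the documents. It runs from 5% (one joint SBP test), through at most 9.75% (one joint test each for SBP and DBP), to roughly 19-24% (6 tests) and 38-49% (18 tests). The last two ranges apply only if terms are tested separately, any one suffices, and the correlations lie in the ranges assumed above. The sample size calculation itself is not at fault.

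**What to change.** 1. State SBP as the single primary outcome, in the same words, in the Abstract, Section 2.2 and Section 2.4.1. Make DBP secondary.
2. In Section 2.6, name one deciding test that matches the sample size: the three-group omnibus comparison of SBP change from baseline at one named visit, for example T2, the three-month post-test. T3 and T4 become secondary.
3. Test the three pairwise contrasts, including Tai Chi versus walking, each at 0.05 and only if the omnibus test is significant. With three groups this is a closed procedure: if any two pairwise nulls are true, so is the third, and the omnibus test guards that case. The overall error stays at 5%.
4. Do not make Tai Chi versus walking the gatekeeper in a fixed sequence. At about 35% power it would stop the sequence roughly 65% of the time and so block Tai Chi versus control, which has about 89% power.

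**Cost.** No extra patients or data; the change is to the text and should be made before outcome data are seen by group. DBP, T3 and T4 can then no longer carry the primary claim. The change does not raise the low power for Tai Chi versus walking, so a non-significant result there should not be read as evidence that the two exercises are equivalent.

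### The 80% power stated for 61 per arm does not apply to the stated main comparison, Tai Chi versus brisk walking, which has about 35% power on the plan's own 5.75 mmHg and SD 20

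*Protocol article*

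**What the plan says.** The aim is the comparison of the two exercises. The Abstract states: "This protocol aims to evaluate the effectiveness of Tai Chi versus brisk walking in reducing CVD risk factors". It expects that "Tai Chi will be more effective than brisk walking in reducing CVD risk factors". The Introduction repeats that "this study aims to compare the effects of Tai Chi with brisk walking in reducing modifiable CVD risk factors", and the Conclusions give the same overall aim.

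The section Sample Size and Randomization fixes the outcome: "SBP is therefore being set as the primary outcome and for sample size calculation". The calculation is based on "discriminating among a mean SBP reduction of 15.5 mmHg in the Tai Chi group, 4.0 mmHg in the control group". For the third arm, the value is set midway between these two: "9.75 mmHg (the grand mean) in the walking group". The spread is then chosen as follows: "Further conservatively assuming an SD of 20.0". The result is that "G*Power gives that 61 subjects per arm will be needed to achieve a power of 80% at a significance level of 5" per cent. Allowing for 25% attrition, the target becomes 82 per arm, 246 in total.

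The section does not name the test behind the 61 and gives no power for any pair of arms. Section 2.6 plans GEE models with group-by-time terms and the control group as reference.

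**The concern.** The article offers one power figure and one headline question, and a reader will naturally connect them. The sizing inputs suggest that they do not belong together. Putting walking at the midpoint between Tai Chi and control halves the assumed difference for the comparison of interest (5.75 mmHg, against 11.5 mmHg for Tai Chi versus control). A global test of three means then draws its power mainly from the two outer arms.

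What is at stake is how the primary result is read. The Introduction and Conclusions say it would matter if Tai Chi proved as good as walking or better. A trial with low power for that pair can easily end with a non-significant difference, which could then be taken as evidence that the two are alike. The Discussion itself notes that earlier null Tai Chi studies were hard to interpret because of limited power.

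**Working it through.** **Inputs (Sample Size and Randomization).** Mean SBP reductions: 15.5 (Tai Chi), 9.75 (walking), 4.0 (control) mmHg. SD 20. Significance level 5%; sidedness is not stated, so two-sided is assumed for pairs. 61 evaluable per arm; 82 per arm recruited.

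**Step 1: reproduce the 61.** The mean of the three means is 9.75, so the deviations are 5.75, 0 and −5.75.

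- Effect size: f = √[(5.75² + 0 + 5.75²)/3] / 20 = 4.695/20 = 0.235.
- One-way ANOVA F test, noncentrality λ = 3n·f², df 2 and 3n − 3:

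| n per arm | λ | Power |
|---|---|---|
| 59 | 9.75 | 79.8% |
| 60 | 9.92 | 80.5% |
| 61 | 10.08 | 81.2% |

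The minimum is 60 per arm against 61 stated. Attrition: 61/0.75 = 81.3, rounded up to 82 per arm, 246 in total, as stated.

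**Step 2: try other routes to 61.** A two-sample t test of 11.5 mmHg at SD 20 needs 49 per arm at a level of 0.05, 59 at 0.025 and 65 at 0.05/3. The 0.025 version is also close, but the section mentions no split of the significance level. A two-sample test of 5.75 mmHg needs 191 per arm, so no such test for Tai Chi versus walking gives 61.

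**Step 3: power by pair.** Two-sample t test of mean change, two-sided 5%, noncentrality δ = difference / (SD·√(2/n)). At n = 61 the standard error is 20·√(2/61) = 3.62; at n = 82 it is 20·√(2/82) = 3.12.

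| Comparison | Difference (mmHg) | δ at 61 | Power at 61 | Power at 82, no dropout |
|---|---|---|---|---|
| Tai Chi vs walking | 5.75 | 1.59 | 35% | 45% |
| Walking vs control | 5.75 | 1.59 | 35% | 45% |
| Tai Chi vs control | 11.5 | 3.18 | 88% | 96% |

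**Step 4: sensitivity to the SD, Tai Chi versus walking, 61 per arm.** The section quotes SDs of 7.9 and 10.5 (Tai Chi and control arms of the local study) and 15.6 (walking study). The root mean square of the Tai Chi and walking values is √[(7.9² + 15.6²)/2] = 12.4. The two source means differ by 15.6 − 8.7 = 6.9 mmHg.

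| SD | Power, 5.75 mmHg | Power, 6.9 mmHg |
|---|---|---|
| 20 (planning value) | 35% | 47% |
| 15.6 | 52% | 68% |
| 12.4 (illustrative) | 72% | 86% |
| 10.5 | 85% | 95% |

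For 5.75 mmHg, 80% power at 61 per arm requires an SD of about 11.2 to 11.3.

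**Step 5: what 61 per arm can show at SD 20.** The Tai Chi versus walking difference detectable with 80% power is about 10.2 mmHg. The expected 95% CI half-width is 1.98 × 3.62 = 7.2 mmHg, wider than the 5.75 mmHg assumed.

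**The case against.** The strongest defence is that nothing is miscalculated. The section says it sizes the trial to discriminate among three means, lists every input and never attaches the 80% to Tai Chi versus walking. Sizing a three-arm trial on a global comparison is a recognised choice and fits an analysis that compares changes among three groups. This stands: the fault is a mismatch between aim and stated power, not faulty arithmetic.

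Second, SD 20 is called conservative and exceeds every SD the section quotes. With SD 12.4 and the 6.9 mmHg difference between source means, power is 86%. This stands in part. The 35% is the SD 20 case, and a reader might infer that two trials in three are bound to miss a Tai Chi versus walking difference; that follows only if the conservative SD is also the expected one. On the other hand, the stated 80% rests on that same SD 20. The 12.4 also combines two different studies, one of them in obese postmenopausal women, so it is illustrative only.

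Third, two further readings go too far. One might treat the omnibus F test as established; the section names no test, and the match is 60 against 61, so it is a strong inference. One might also say the 80% fails for all the group-by-time coefficients in Section 2.6. With control as reference, some of those coefficients are Tai Chi versus control, for which the simple comparison has about 88%. The shortfall concerns Tai Chi versus walking and walking versus control.

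Finally, the GEE uses partial data from dropouts, so a completers-only figure may be somewhat low. Full retention of 82 per arm still gives only 45% at SD 20, and the section assumes no baseline correlation from which a further gain could be claimed.

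**Conclusion.** The point holds as a mismatch between the stated power and the stated main question. On the planning values (5.75 mmHg, SD 20, two-sided 5%, simple comparison of mean change), power for Tai Chi versus walking is about 35% at 61 per arm and 45% at 82 per arm. This does not depend on which test produced the 61. Across the SDs and differences drawn from the section's own figures in Step 4, power at 61 per arm runs from 35% to 95%; the values above 80% need an SD well below the planning value. At SD 20, a non-significant difference between the two exercises would not show that they are alike, because the interval is expected to extend about 7.2 mmHg either side of the estimate.

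**What to change.** In Sample Size and Randomization, add one paragraph that:

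- names the test to which the 80% at 61 per arm belongs;
- states the power for Tai Chi versus walking: about 35% at 5.75 mmHg and SD 20, with the SD sensitivity (52% at 15.6, about 72% at 12.4 marked as illustrative, 85% at 10.5), alongside about 88% for Tai Chi versus control;
- states the Tai Chi versus walking difference detectable with 80% power (about 10.2 mmHg at 61 per arm) and the expected 95% CI half-width (about 7.2 mmHg);
- states that a non-significant Tai Chi versus walking result will not be interpreted as showing that Tai Chi is as good as walking.

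This costs one paragraph and needs no change in enrolment, arms or analysis. The downside is a less favourable stated power for the main comparison.

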#### 2.3.3. Control Group

Participants in the control group will be advised to maintain their routine activities. No extra exercise will be recommended. During the study period, all subjects will continue their prescribed medical treatments, if any. To enhance the internal validity of the study findings, participants in the walking and control groups will be arranged to join non-health-related social activities regularly for three months. The purpose of maintaining regular gatherings for the participants is to balance the psychosocial effect of weekly gatherings of the Tai Chi group during the process of Tai Chi training.

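### Allocation as described leaves balance on clinic and BP medication to chance, and the significance-triggered adjustment misses most moderate imbalances: a small loss, cheap to remove

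*Protocol article*

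**What the plan says.** Four parts of the protocol article bear on this point.

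- **Source population (2.1. Subjects).** "Potential subjects will be recruited from two outpatient clinics". The BP entry criterion is met by SBP or DBP above a threshold, "or are taking blood pressure medication". Treated patients therefore enter whatever their current reading. The shares by clinic and by treatment are not given.
- **Treatment during the study (2.3.3. Control Group).** "all subjects will continue their prescribed medical treatments, if any".
- **Allocation (Sample Size and Randomization).** "Eligible subjects will be randomly assigned to the three groups in 1:1:1 ratio according to their sequence of enrolment into the study". Each participant is matched to the next entry on a sequence generated beforehand, and the sequence is spoken of in the singular: "The random group identifiers list will be stored in a password-protected computer". No strata, blocks or minimisation are described.
- **Analysis (2.6. Data Analysis).** Baseline characteristics are compared across the three groups by chi-square test or one-way ANOVA. The GEE models are then fitted "with adjustment for those baseline characteristics showing statistically significant differences among the groups". The treatment effect is read from the interaction with time, with baseline as the reference visit: "The interaction-terms of group by time will also be included in the GEE models". Clinic and BP medication are not named as covariates.

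**The concern.** Clinic and BP medication are both known before randomisation, and either could plausibly be related to how far SBP changes. Patients who enter on a BP threshold are exposed to regression to the mean. Patients who enter because they take medication need not be. If the arms differ by chance in their share of treated patients, and treated and untreated patients change by different amounts, the SBP contrasts in that particular trial are displaced.

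The smallest contrast of interest is Tai Chi versus walking, planned at 15.5 − 9.75 = 5.75 mmHg, so even a shift of 0.5 to 1 mmHg is visible there. The plan's only safeguard is a rule that adjusts after a significant baseline test. Such a test responds to sample size and not to whether a covariate matters for the outcome, so moderate imbalances would usually pass unadjusted. Moreover, a covariate entered as a time-constant term does not act on a group-by-time effect.

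**Working it through.** **Inputs from the protocol article.** Three arms, 1:1:1; assumed SBP reductions 15.5, 9.75 and 4.0 mmHg; SD 20.0; 61 per arm for 80% power at 5%; 25% attrition; 82 per arm; 246 in total.

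**Inputs assumed.** Share on BP medication p = 30% to 85%; difference in SBP change between treated and untreated patients δ = 3, 5 or 10 mmHg; exactly 82 per arm; SD 20 taken as the SD of the SBP contrast variable. The article gives none of these shares or differences.

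**1. The plan's own figure.** The deviations from the grand mean are +5.75, 0 and −5.75. So f = √[(5.75² + 0 + 5.75²)/3]/20 = 4.695/20 = 0.2347. The one-way ANOVA F test then has 80.5% power at 60 per arm and 81.2% at 61. The stated 61 is reproduced to within one patient. 61/0.75 = 81.3, rounded up to 82 per arm, gives 246.

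**2. How often the arms differ.** The SD of the difference in medicated share between two arms is √[2p(1−p)/82]. This is 7.8 points at p = 50%, 7.2 at 30% or 70%, and 5.6 at 85%. In 20,000 simulated allocations:

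| Share on medication | Some pair differs by at least 10 points | Of these, chi-square not significant |
|---|---|---|
| 50% | 38% | 87% |
| 30% or 70% | 31% | 85% |
| 85% | 15% | 66% |

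For one given pair, such as Tai Chi versus walking, a gap of at least 10 points occurs in about 18% of allocations at p = 50%.

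**3. Where the baseline test fires.** At p = 50% the statistic is Σd²/(82 × 0.25), where d is each arm's deviation from the mean count, and the critical value is 5.99. The smallest range r (in patients) that can be significant occurs when two arms share one extreme. Then Σd² = 2r²/3, so r = √(1.5 × 5.99 × 20.5) = 13.6. That means 14 of 82, or 17 points. As an example below the trigger, 41, 45 and 49 of 82 is a gap of 8/82 = 9.8 points. It gives 32/(82 × 0.549 × 0.451) = 1.58 on 2 df, p = 0.45.

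**4. Size of the shift.** Shift = gap × δ. A 10-point gap with δ = 5 to 10 gives 0.5 to 1.0 mmHg, which is 9% to 17% of 5.75. The root-mean-square shift over allocations at p = 50% is δ × 0.0781, or 0.23, 0.39 and 0.78 mmHg for δ = 3, 5 and 10. The standard error of a pairwise contrast is 20 × √(2/82) = 3.12 mmHg.

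**5. What removing it gains.** The share of variance is δ² × 0.25/400, or 1.6% for δ = 5 and 6.3% for δ = 10. The residual SD falls to √(400 − 6.25) = 19.84 or √(400 − 25) = 19.36. Omnibus power at 61 per arm rises from 81.2% to 81.8% or 83.8%.

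**6. Which model term does the correcting.** GEE fits used an exchangeable correlation and group × time terms. In one complete simulated dataset the group-by-time estimate was −2.614 both without the covariate and with its main effect. In 300 simulated trials there was a forced 20-point imbalance (50%, 70% and 60% medicated), a 5 mmHg difference in change, no true group effect and about 15% of post-baseline values missing. The expected shift is 0.20 × 5 = 1.0 mmHg. Mean bias (simulation standard errors 0.17 to 0.18) was:

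- unadjusted: 1.06 mmHg
- covariate main effect: 1.06 mmHg
- covariate × time: 0.01 mmHg

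**The case against.** The strongest reply is that nothing here is an error. An unstratified list is a legitimate design and is unbiased over repeated randomisation. The variation from chance imbalance is already contained in the standard error, and a shift of 0.4 to 0.8 mmHg is only 12% to 25% of that standard error. Quoting the shift as a fraction of 5.75 mmHg alone makes it look larger than it is. This stands, and it limits the point to efficiency and robustness.

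The size also rests on assumed figures. At 85% medicated, the chance of a gap of at least 10 points is 15% and not 38%. The difference must be in SBP change: a pure level difference between clinics or between treated and untreated patients cancels against baseline. No magnitude can be put on clinic at all. This also stands.

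A reader might infer that the article states allocation is unstratified. It does not. That is the natural reading of a single list used in enrolment order, but the article is condensed and the full protocol may add strata or blocks.

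A reader might also infer that the adjustment rule can never correct an imbalance. That is too strong. The rule would act on a large imbalance if these factors are among those tested, and the article does not fix whether a covariate enters with a time interaction. What remains is that the trigger, as written, passes over most moderate imbalances.

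**Conclusion.** The point holds as a minor improvement. As described, allocation leaves balance on clinic and BP medication to chance. The significance-triggered rule would leave about 87% of gaps of at least 10 points unadjusted at an assumed 50% medicated (66% to 85% at the other shares examined).

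The benefit of repair is small: at most a few points of omnibus power, and that only if SBP change really differs by 5 to 10 mmHg between treated and untreated patients. The documents do not support a claim that the planned comparison is invalid or biased. The better-founded part of the point is the analysis rule, because it is stated explicitly and selects covariates by baseline tests.

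**What to change.** **In either case.** Replace the significance-triggered rule for these two factors. Prespecify clinic and baseline BP medication (yes/no) in every GEE model, each with its interaction with time, whatever the baseline tests show. With four visits this is one main effect and three interaction terms per factor, eight coefficients in all. Entering them as main effects only would not serve the purpose.

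**If allocation has not begun.** Also generate separate permuted-block lists for the four strata of clinic by BP medication at entry, with varying block sizes that are concealed from recruiting staff. If allocation has begun, keep the existing list and rely on the model terms.

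**Cost.** Four lists to manage instead of one, and a few more model terms. Participants cannot be blinded, so small blocks add some predictability: in a block of three, the last assignment follows from the first two. Varying and concealing the block sizes limits this.
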